## 3.4 Sample size and power calculation

With changes in BP as the primary outcome we calculated a sample of 52 between the 2 groups to show changes in BP between the intervention and control groups at a significance level of 0.05 for a two-sided test with 80% statistical power of finding a large effect (*Cohen’s d*=0.80). This study will be underpowered to find significantly small effect (*Cohen’s d*=0.30) and moderate effect (*Cohen’s d*=0.50), however, we will be able to calculate an effect size and the direction of its impact.

## 3.5 Sampling and participants recruitment

We will randomly sample 2 wards in Ruiru and Juja Sub-counties. All participants in the selected wards with uncontrolled BP willing to participate will be recruited into the study. Screening will be done at the community level. CHW will conduct door to door screening for hypertension using digital BP machines for all adults in the selected wards. The CHW will document the BP readings and anthropometric measurement in a paper form register. The CHW will offer a referral letter (to the nearest level 3 hospital) for all participants with uncontrolled BP. The CHW will furnish the study coordinator with the particulars of such participants for follow-up and possible recruitment into the study. Participants will receive a refund of the transport cost upon presenting the referral note so as to encourage them to turn up at the health facility. Participants who do not show up in the facility within 48 hours of screening will be traced through home visits. The participants will be recruited for the RCT at the level 3 health facility in the respective wards after reassessment by the clinician and commencement of medical management.

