# Abstract

In Sub Saharan Africa (SSA) there is a growing burden of Non communicable diseases (NCDs) which poses a big challenge to the weak health system in these resource limited settings. As governments prioritize the control of the COVID 19 pandemic, consequences of chronic diseases such as cardiometabolic risk factors (CMRFs) continue unabated. The aim of this study is to explore innovative strategies to improve blood pressure and body composition through community health workers lifestyle interventions among hypertensive patients in low income populations of Kiambu County, Kenya.

This will be a community-based study which will begin with home-based blood pressure(BP) screening by community health workers (CHW). Those identified as hypertensive will then be recruited to a randomized control trial. The randomized controlled trial (RCT) will involve 52 hypertensive patients willing to be followed up for 6 months. The patient will be randomised to either CHW led lifestyle intervention or usual care arm. The intervention will be implemented for 6 months with outcome assessment at 3 and 6 months. The recruitment will be conducted in level 3 primary health care facilities in Juja and Ruiru Sub-counties in Kiambu County.

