**1.1 Problem statement**

Hypertension is the leading risk factor for deaths due to CVDs and as such, the World Health Organization (WHO) targets to have a worldwide 25% reduction in the prevalence of hypertension by the year 2025 (World Health Organization, 2014). The STEPwise survey shows 24% of Kenyans either had elevated BP or were on treatment for hypertension. Only 8% of the hypertensive persons were on treatment, and among them, only 4.6% had controlled BP (Kenya Ministry of Health, 2016).

Based on literature, modi­fication of lifestyle factors can delay onset of hypertension and can contribute to lowering of BP in treated patients (Gabb et al., 2016; Whelton et al., 2002). Systematic reviews have shown efficacy of interventions focused on physical inactivity (Pescatello et al., 2019; Smart et al., 2020) and dietary approaches to stop hypertension (DASH) (Filippou et al., 2020; Saneei et al., 2014; Siervo et al., 2015) in lowering BP among adults with or without hypertension in different settings. However, we do not know the acceptability of these behavioural interventions in the control of hypertension in Kenya. Clinical trials have also demonstrated the effectiveness of community based CHW interventions in lowering BP among both hypertensive patients(He et al., 2017; Jafar et al., 2010) as well as non-hypertensive population(T. H. Jafar et al., 2009; Neupane et al., 2018) in resource limited settings.

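### Co-residents can be randomised to opposite arms of a home-delivered intervention: section 3.5 recruits every willing adult with uncontrolled BP, and no household rule exists

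*Protocol*

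**What the plan says.** Protocol section 3.5 sets both the screening frame and the recruitment rule. On screening: "CHW will conduct door to door screening for hypertension using digital BP machines for all adults in the selected wards". On recruitment: "All participants in the selected wards with uncontrolled BP willing to participate will be recruited into the study". The wards are chosen at random ("We will randomly sample 2 wards in Ruiru and Juja Sub-counties"), and their population is not given. People found to have uncontrolled BP are referred to a level 3 facility. Their details go to the study coordinator, and enrolment takes place at the facility after a clinician has reassessed them.

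Section 3.1 makes the individual patient the unit of randomisation. Section 3.8 places the intervention in the home: a first visit of 90 minutes with lifestyle counselling and activity targets, then monthly visits for support, goal setting and BP review. Section 3.3.2 excludes only people older than 70 and people planning to move away. No section limits enrolment to one person per household, allocates households as units, or says how relatives are handled.

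The size of the trial is fixed elsewhere. The Abstract says: "The randomized controlled trial (RCT) will involve 52 hypertensive patients willing to be followed up for 6 months". Section 3.4 says: "we calculated a sample of 52 between the 2 groups".

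**The concern.** Screening everyone at home and recruiting every willing person with uncontrolled BP means that, where two adults in one household qualify, the plan as written enrols both. Individual randomisation can then give one of them the CHW programme and the other usual care under the same roof. Counselling on lifestyle and BP delivered at home is easily overheard, shared or acted on by the whole household. The control may improve because of the intervention, and the difference between arms shrinks.

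This matters beyond power. The trial is meant to give a preliminary effect estimate for a later, fully powered RCT (section 1.2), and a diluted estimate would carry into that design. A statistical analysis plan cannot repair it, because contamination is settled at enrolment and allocation.

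A second, smaller matter is that the recruit-all sentence has no closing point, although the Abstract and section 3.4 fix the total at 52.

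**Working it through.** **Inputs from the protocol.** Total 52, two-sided alpha 0.05, 80% power, d = 0.80 (section 3.4); 24% with elevated BP or on treatment, 8% of hypertensives treated and 4.6% of those controlled (section 1.1).

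**Assumed.** 1:1 allocation, so 26 per arm, because the ratio is not stated; the share f of controls living with an intervention participant; the fraction g of the effect that such a control gains.

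**1. The plan's own figure.** A two-sample t-test at d = 0.80 needs 25.52 per arm, so 26 per arm and 52 in total. With 26 per arm the noncentrality is 0.80 × √(26/2) = 2.88, and power is 80.7%. The 52 is correct for its inputs.

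**2. Chance that a co-resident pair is split.** Fix one member's arm. Of the other 51 places, 26 are in the opposite arm, so the probability is 26/51 = 0.51. With three such pairs, treated as independent, the chance of at least one split is 1 − (25/51)³ = 0.88.

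**3. Illustrative dilution.** Diluted d = 0.80 × (1 − f × g). With f = 0.10 and g = 0.5, d = 0.80 × 0.95 = 0.76. The noncentrality becomes 0.76 × √13 = 2.74, and power is 76.6%.

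**4. How many pairs that illustration needs.** With k pairs, the expected number of split pairs is k × 26/51. Each contributes one control, so f = (k × 26/51)/26 = k/51.

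| f | pairs k = 51f | participants in pairs | share of 52 | diluted d (g = 0.5) | power |
|---|---|---|---|---|---|
| 10% | 5.1 | about 10 | 20% | 0.76 | 77% |
| 20% | 10.2 | about 20 | 39% | 0.72 | 72% |
| 30% | 15.3 | about 31 | 59% | 0.68 | 67% |

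Only the first row is used below. The others need an implausible share of the trial to be paired relatives.

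**5. Recruit-all against 52.** Uncontrolled prevalence = 0.24 × (1 − 0.08 × 0.046) = 0.239. Adults screened to fill 52 places = 52/(0.239 × share willing and eligible), using the unrounded prevalence: 217 at 100%, 435 at 50%, 870 at 25% and 2,175 at 10%. The willing share and the number of adults in the wards are not in the protocol, so this gives a range and does not prove a conflict.

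**The case against.** **Frequency.** Nothing in the protocol shows that relatives would often enter together. Both must have raised BP on at least two separate measurements, be willing, be no older than 70, attend the facility and pass reassessment. This stands: co-enrolment is possible, but its frequency is unknown. Even the 10% case needs about one participant in five to be in a same-household pair, and it costs about four points of power in a study that already calls itself underpowered for moderate and small effects.

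**The total of 52.** A reader might infer that the recruitment rule cannot be met. The documents do not support that, because ward size and willingness are not given. The 217 is a floor resting on a national figure that includes treated people. Ward-wide screening also has its own purpose, the prevalence objective in section 2.3, and closing enrolment at the target is the ordinary reading. What stands is a loosely worded sentence without a stopping point. For the same reason it cannot be claimed that eligible people far exceed 52.

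**Selection by CHWs.** A reader might also infer that the first streets visited would fill the trial and distort the baseline-risk objective. Section 3.5 does not say so: CHWs screen and pass on details, and recruitment happens at the facility.

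**Equipment and analysis.** Sharing of BP devices is not established, since section 3.8 does not say that one stays in the home. Nor can the analysis be said to ignore correlation between relatives: section 3.9 names GEE without stating the clustering unit, a detail that the statistical analysis plan may settle.

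None of this removes the core point. Section 3.5 as written calls for enrolling every willing eligible member of a home, and nothing keeps them in the same arm.

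**Conclusion.** The point holds as a gap in the design that is cheap to close. Recruitment of all willing adults, individual randomisation, home delivery and the absence of a household rule together allow co-residents to fall in opposite arms, with probability 0.51 per pair under an assumed 26:26 split. The direction of bias is toward no difference, on the premise that a control benefits from counselling given in the same home. Its size cannot be derived from the documents. With 10% of controls exposed and half the effect gained, both assumed, d falls from 0.80 to 0.76 and power from about 81% to 77%. The tension between recruiting all and a total of 52 is a matter of wording and is not shown to be an impossibility.

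**What to change.** Amend section 3.5 to say that enrolment closes once 52 participants are enrolled, and that only one eligible adult per household enters the trial, picked at random where several qualify. Everyone else with uncontrolled BP is referred exactly as the section already provides. If the investigators prefer to allow more than one member, state that the household is allocated as one unit, and in section 3.9 that the GEE clusters on household.

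The cost is a few sentences, a household identifier on the screening register, and a slightly smaller eligible pool. Approaching the whole register in random order is not recommended: screening would have to finish before the first enrolment, which conflicts with the 48-hour tracing and the facility-based recruitment in section 3.5.

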## 2.3 Specific Objectives

i. To determine the prevalence of hypertension among adults in selected wards in Kiambu County.

ii. To determine the baseline cardio-metabolic risk among hypertensive patients in Kiambu County.

iii. To determine the effectiveness of a multicomponent CHW lifestyle intervention for control of BP among hypertensive patients in Kiambu County.

iv. To determine the acceptability of a multicomponent CHW lifestyle intervention for control of blood pressure among hypertensive patients in Kiambu County.

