## 3.6 Data collection

An adapted WHO stepwise questionnaire will be used to collect information on demographic characteristics (age, sex, occupation), history of hypertension, other CVD risk factors, and health behaviours (smoking, alcohol drinking, diet, and physical activity) of participants at baseline and follow-up visits. The international physical activity questionnaire (IPAQ)(Craig et al., 2003) will be used to collect data on physical activity. The tools will be translated and validated in the local context. We will collect detailed data on patients care cascade during the home visits and monitor their ability to control their BP with the combination of medical management and the CHW intervention. Three BP measurements, body weight, height and waist circumference will be obtained at each data collection visit by outcome assessors masked to intervention assignment.

The primary outcomes will be the differences in systolic and diastolic BP changes from baseline to the end line survey. Secondary outcomes will include the proportion of patients with controlled hypertension (BP <140/90 mm Hg) ) according to the Kenyan national guidelines(Division of Non-Communicable Diseases-Ministry of Health, 2018), body composition – Body mass index(BMI), waist circumference . Low physical activity will be defined as less than 150 minutes of moderate physical activity or 75 minutes of vigorous activity each week. To assess the outcome of the intervention the survey conducted at baseline will be conducted at 3 months of follow-up and at the end of 6 months of intervention.

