## 3.8 Study procedure

The study coordinator and the research assistants will complete a baseline assessment for the illegible participants. This will involve a survey to collect sociodemographic variables, measuring BP, anthropometric measurements (Height, weight and waist circumference) and lifestyle behaviour. Patients with uncontrolled blood pressure will be randomized either control arm (usual care) or intervention arm (Figure 1). The intervention will include a multicomponent community health worker–led home intervention (health coaching, home BP monitoring, BP audit and feedback, physical activity program to be implemented over a period of six (6) months. Participants randomized to the intervention will receives 2 home visits by the trained CHW over a period of 1 month, followed by monthly follow-up visits for a period of 6 months. The initial visit will involve a 90-minute home visit to discuss general knowledge about hypertension and offer tailored counselling on lifestyle modification as well as set physical activity targets. Subsequent monthly visit will be focused on social support, goal setting, problem solving, and maintaining motivation to meet set targets. The visits will involve BP monitoring during which the client and CHW will evaluate the BP and physical activity targets.

To assess the outcome of the intervention the survey conducted at baseline will be conducted by two trained research assistants (who were not part of and have no relationship with the CHWs team) to evaluate the participants at 1) 3 months and 2) 6 months when the intervention has ended. The research assistants will be blinded to the randomization status of the participants. The home visits/clinic visit for evaluation will be scheduled during the first half of the day to minimize the effect of diurnal variations in BP.

Materials to be used will include automatic BP machine, tape measure, a bathroom weighing scale, smart watch fitness monitor and a smart phone with intervention protocol detailing the health education on lifestyle intervention for reducing BP. A paper-based protocol will also be provided for back-up.

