|  | *The last question is about the time you spent sitting on weekdays during the last 7 days. Include time spent at work, at home, while doing course work and during leisure time. This may include time spent sitting at a desk, visiting friends, reading, or sitting or lying down to watch television*.  During the last 7 days, how much time did you spend sitting on a week day? | 1.…………… hours per day  2……………. minutes per day  Don’t know/Not sure |
| **History of Raised Blood Pressure** | | |
|  | Have you ever had your blood pressure measured? |  |
|  | Have you ever been told by a doctor or other health worker that you have raised blood pressure or hypertension? |  |
|  | Are you on any treatments/advice for high blood pressure? | |
|  | Drugs (medication) that you have taken in the past two weeks |  |
|  | Advice to reduce salt intake |  |
|  | Advice or treatment to stop smoking |  |
|  | Advice to start or do more exercise |  |
| **Step 2 Physical Measurements** | | |
|  | Interviewer ID |  |
|  | Device IDs for height and weight |  |
|  | Height(cm) |  |
|  | Weight(kg) |  |
|  | **For women:** Are you pregnant? |  |
|  | Waist circumference(cm) |  |

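### Objective i asks for the prevalence of hypertension, but the screening register as described supports only the prevalence of raised blood pressure (minor)

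*Protocol*

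**What the plan says.** Section 2.3 of the protocol gives as its first objective: "To determine the prevalence of hypertension among adults in selected wards in Kiambu County". Research question 1 in section 2.1 asks the same.

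Section 3.5 describes how the wards are covered: "CHW will conduct door to door screening for hypertension using digital BP machines for all adults in the selected wards". It then says what is written down: "The CHW will document the BP readings and anthropometric measurement in a paper form register". The next step applies to one group: "The CHW will offer a referral letter (to the nearest level 3 hospital) for all participants with uncontrolled BP". Section 3.3 sets the threshold for that group at 140 mmHg systolic and/or 90 mmHg diastolic, on at least two separate screening measurements.

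History of hypertension is collected with the adapted WHO questionnaire. Section 3.6 says it covers these topics "of participants at baseline and follow-up visits", and section 3.8 places the baseline survey at recruitment: "The study coordinator and the research assistants will complete a baseline assessment for the illegible participants" (evidently a slip for eligible). The questionnaire in Appendix 2 asks whether a health worker has ever told the respondent that their blood pressure is raised. Under treatment for high blood pressure it has the item "Drugs (medication) that you have taken in the past two weeks".

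The background in section 1.1 quotes a national survey in which "24% of Kenyans either had elevated BP or were on treatment for hypertension".

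**The concern.** A prevalence of hypertension normally includes people whose hypertension is known and under control. The national figure quoted in section 1.1 does so, because it counts being on treatment as well as a raised reading. To count such people, the screening visit has to ask about treatment or diagnosis.

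As section 3.5 describes it, the visit yields blood pressure and body measurements. The questions that would identify treated adults come later, and only for people already selected because their blood pressure is uncontrolled. Adults with treated, controlled hypertension never reach that questionnaire.

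At stake is whether the result reported for objective i is the quantity the objective names. This is a question of data capture. A later analysis plan can define hypertension as it likes, but it cannot supply a treatment variable that was not collected, and recovery would mean going back to the households.

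**Working it through.** **Step 1: can the data identify a treated, controlled adult?** There are three kinds of adult at the door:

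| Adult screened | Reading | In the register as described | Reaches Appendix 2? |
| --- | --- | --- | --- |
| Normotensive | below 140/90 | normal reading | no |
| Hypertensive, treated and controlled | below 140/90 | normal reading | no |
| Hypertensive, uncontrolled (treated or not) | at or above 140 and/or 90 | raised reading | yes, if recruited |

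The first two rows are identical in everything the protocol says is recorded. The count that can be formed is the third row, which is raised blood pressure at screening.

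**Step 2: how large is the difference?** The protocol states no expected prevalence and no sample size for objective i, so there is no planned figure to reproduce. The nearest benchmark is the 24% in section 1.1, which includes people on treatment.

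Inputs:
- P = 24%, raised reading or on treatment (section 1.1).
- 8% of hypertensive persons treated, and 4.6% of those controlled (section 1.1).
- 7.7% of hypertensive patients controlled to below 140/90 in LMICs (Background Information).

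Let c be the share of hypertensive adults who are treated and controlled. The count loses P × c and reads P × (1 − c).

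| Basis for c | c | Points lost, 24 × c | Count would read |
| --- | --- | --- | --- |
| Section 1.1 as worded: 0.08 × 0.046 | 0.00368 | 0.09 | 23.9% |
| 4.6% taken as a share of all hypertensives | 0.046 | 1.10 | 22.9% |
| LMIC control rate | 0.077 | 1.85 | 22.2% |
| Ceiling: all of the 8% treated are controlled | 0.08 | 1.92 | 22.1% |

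The second row allows for the possibility that the 4.6% was meant as a share of all hypertensive persons. The fourth is the most that section 1.1 permits, since no more people can be treated and controlled than are treated. In general, each additional 1% of hypertensive adults who are treated and controlled removes 24 × 0.01 = 0.24 points.

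**The case against.** **The register may hold more than the sentence lists.** Section 3.5 does not say that nothing else is recorded. The CHW must also pass on the particulars of people with uncontrolled blood pressure and must know who is an adult, so the description is evidently a summary, and the form itself is not in the protocol. This stands as a limit: the finding concerns the register as described. A reader might infer that treatment history is definitely not collected at the door, and the text does not go that far.

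**Appendix 2 may be meant for everyone.** Its title speaks of prevalence of risk factors in a low-income population, and it asks whether blood pressure has ever been measured, which suits a general adult sample. Section 3.5 also uses the word participants for people still at the screening stage. There is some ambiguity here, but sections 3.6 and 3.8 tie the questionnaire to baseline and follow-up assessments, which come after selection. The care-cascade data mentioned in section 3.6 do not help either. They come from home visits to patients whose blood pressure is being followed under medical management and the CHW intervention.

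**The case definition belongs in an analysis plan.** That is fair for the definition alone, and its absence here is not a finding. It does not answer the data-capture point.

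**The effect is negligible.** On the most direct figures it is about 0.1 point. This stands and sets the severity.

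**Conclusion.** The point holds as a minor mismatch between an objective and the data described for it. Followed as written, the screening would give the prevalence of raised blood pressure at screening. On the protocol's figures that is 0.1 to 1.9 points below a 24% prevalence that includes people on treatment. This assumes that the national and LMIC figures apply to the selected wards, for which the protocol gives no data, and that the register holds what section 3.5 lists. The randomised comparison does not depend on it.

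Four stronger conclusions might be inferred, and the documents do not support them:
- That the undercount is large. It would require far more than the 8% treated share in section 1.1.
- That the ward estimate is biased downward overall. Only one component is examined here. Section 3.5 provides for reassessment by a clinician, so some raised screening readings may not be confirmed, which would push the other way.
- That a planned comparison with the 24% fails. The definitions do differ, but the 24% is background and no such comparison is planned.
- That required estimates of awareness, treatment and control are lost. Ward-level estimates of these are not among the four specific objectives.

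**What to change.** In section 3.5, add two existing Appendix 2 items to the CHW register for every adult screened: whether a health worker has told them their blood pressure is raised, and whether they have taken drugs for it in the past two weeks. For objective i, count an adult as hypertensive if screening blood pressure is at or above 140 systolic and/or 90 diastolic, or if they currently take antihypertensive drugs. Report raised blood pressure at screening as a separate line.

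If the register already captures treatment, a sentence in section 3.5 saying so is enough. If it does not and the sponsor prefers not to add the items, rename objective i and research question 1 as the prevalence of raised blood pressure at screening.

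The cost is two tick-boxes on a paper form and about a minute per adult, at a visit already planned, with no extra staff or procedure. The items have to be in place before door-to-door screening starts.

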## 3.7 Data for feasibility and acceptability assessment

At the end of the study, participants in the intervention arm will complete the Client Satisfaction Questionnaire(Larsen et al., 1979) to assess acceptability of the CHW intervention. In addition, 10 patients (purposively sampled to include both gender and different age groups) and CHWs from the intervention group will be targeted for in-depth interviews (IDIs) to understand their experiences and perceptions on the utility of the intervention in the control of hypertension. The IDI guide will cover questions on experiences from using the intervention and determinants of its use. We will assess feasibility of the intervention by examining recruitment rates, follow-up home visits completion rate, dropouts, and adherence to the individualized physical activity program.

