# APPENDIX 2: SURVEY QUESTIONNAIRE

## An adapted WHO stepwise questionnaire to collect prevalence of cardiometabolic risk factors among low income population in Kiambu County.

|  | Phone Number |  |
| --- | --- | --- |
|  | **Demographic Data** | |
|  | Age |  |
|  | Gender | 1. Male 2. Female |
|  | Highest Level Of Education | 1.Never been to school  2.Primary  3.Secondary  4.University/college  5.Other (specify |
|  | Marital status | 1.Single  2.Married  3.Divorced/separated/widowed  4.other (specify) |
|  | Work status over the past 12 months | 1. Employed  2. Self-employed  3. Homemaker  4. Retired  5. Farmer  6.Student  7. Others |
|  | Average earnings of the household for the past 1 year | ---------------------- per day  ----------------------per week  ---------------------per month |
|  | **Behavioural Measurements** | |
|  | Use of Tobacco |  |
|  | Do you use any **tobacco products** i..e cigarettes, cigars or pipes? | 1YES  2 NO |
|  | How often do you smoke cigarette? |  |
|  | At what age did you start smoking cigarette daily? |  |
|  | At what age did you **quit** smoking **daily**? |  |
|  | Do you **use** any **smokeless tobacco** *[snuff, chewing tobacco, betel]*? | 1.YES  2.NO |
|  | How often do you **use smokeless tobacco** |  |
|  | In the past 1 week has someone **in your home** smoked in your presence? | 1. YES 2. NO |
|  | In the past 1 week has someone smoked in closed areas **in your workplace** in your presence? | 1.YES  2.NO |
|  | **Alcohol Consumption** | |
|  | Have you **ever** consumed an alcohol such as beer, wine, spirits, busaa, changaa? | 1.YES  2.NO |
|  | In the past year, have you consumed alcohol? | 1.YES  2.NO |
|  | In the past 1 year how often have you consumed alcohol? | 1 Daily  2 5-6 days per week  31-4 days per week  4 1-3 days per month  5 Less than once a month |
|  | Have you taken alcohol in the past 1 month? | 1.YES  2.NO |
|  | How often have you consumed alcohol with meals | Usually with meals  Sometimes with meals  Rarely with meals  Never with meals |
|  | **Diet** | |
|  | How many days do you **eat fruit in week**? |  |
|  | How many days in a week do you **eat vegetables** |  |
|  | What type of  cooking **oil or fat is used in your household?** | 1.Vegetable oil  2.Butter or ghee  3.Margarine  4. None used  5.Other |
|  | How many meals per week do you eat outside your home |  |

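### Objective i targets all adults in the wards, but the protocol does not provide for counting adults who are absent or refuse, so its prevalence denominator is not secured

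*Protocol*

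**What the plan says.** Protocol section 2.3 gives the first specific objective as "To determine the prevalence of hypertension among adults in selected wards in Kiambu County". The matching fieldwork is in section 3.5: "CHW will conduct door to door screening for hypertension using digital BP machines for all adults in the selected wards". What is written down at that stage is described in one sentence: "The CHW will document the BP readings and anthropometric measurement in a paper form register". For people found with uncontrolled blood pressure (BP), the section adds: "The CHW will furnish the study coordinator with the particulars of such participants for follow-up and possible recruitment into the study". It also has a tracing rule: "Participants who do not show up in the facility within 48 hours of screening will be traced through home visits".

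Age and sex appear in section 3.6, where the adapted WHO questionnaire collects "information on demographic characteristics (age, sex, occupation), history of hypertension, other CVD risk factors, and health behaviours" from participants at baseline and follow-up. Section 3.8 has the study coordinator and research assistants, not the CHWs, carry out the baseline survey. The same questionnaire is printed in Appendix 2, with age and gender items, under a heading that suggests wider use: "An adapted WHO stepwise questionnaire to collect prevalence of cardiometabolic risk factors among low income population in Kiambu County".

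**The concern.** A prevalence among all adults of a ward needs a count of those adults, or at least a record of who was approached and not measured. BP and body measurements exist only for someone who was measured. If nothing else is kept, the proportion computed is among adults who were in and agreed, which is a different population from the one in objective i.

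Adults at home when a CHW calls may well differ in age, sex and work from those who are out, and hypertension varies with such characteristics. If many adults are screened, the confidence interval will be narrow and will reflect sampling error only. A reader would have no response proportion by which to judge the figure. The outcome of a call and the profile of those missed have to be recorded at the door. A later analysis plan can choose weights or intervals, but it cannot supply a denominator that was never collected.

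**Working it through.** **The plan's own figures.** The protocol states no sample size, precision or response rate for objective i. Its one design calculation, 52 participants for a standardised effect of 0.80 at two-sided 0.05 and 80% power, concerns the randomised comparison. It reproduces with the two-sample t-test (26 per arm, power 80.7%) and has no bearing here.

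**Who is covered by each provision.**
- Screening (3.5): aimed at all adults in the wards.
- Register (3.5): content named is BP and anthropometry, so measured adults only.
- Particulars passed to the coordinator (3.5): measured adults with uncontrolled BP only.
- 48-hour tracing (3.5): adults already screened and referred. Adults missed at the door are not covered.
- Age and sex (3.6, 3.8): participants at baseline and follow-up.
- Appendix 2: has age and gender items and a heading that mentions prevalence, but no field for the result of a call. Even if used at every door, it would not count absent or refusing adults.

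No provision counts resident adults who were not measured.

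**Illustration of what could be at stake.** The 24% comes from the national survey figure cited in section 1.1. The response proportion r, the prevalence gap between measured and unmeasured adults, and the number screened are assumptions.

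Bias = (1 − r) × gap:

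| r | gap 5 points | gap 15 points |
|---|---|---|
| 0.80 | 0.20 × 5 = 1 point | 0.20 × 15 = 3 points |
| 0.60 | 0.40 × 5 = 2 points | 0.40 × 15 = 6 points |

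Sampling error with 2,000 screened, treated as a simple random sample: 1.96 × √(0.24 × 0.76 / 2000) = 0.019, or ±1.9 points. The bias exceeds this when the gap is above 1.9 / 0.20 = 9.5 points at 80% response, or above 1.9 / 0.40 = 4.75 points at 60%.

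A second route lets unmeasured adults have 0.5 to 1.5 times the observed 24%. The true value is r × 24% + (1 − r) × k × 24%:
- r = 0.80: 21.6% to 26.4%, a bias of up to 2.4 points either way.
- r = 0.60: 19.2% to 28.8%, a bias of up to 4.8 points either way.

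With no assumption about the unmeasured adults, the bounds are r × 24% to r × 24% + (1 − r): 19.2% to 39.2% at r = 0.80, and 14.4% to 54.4% at r = 0.60.

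**The case against.** The strongest reply is that this argues from silence. The register form is not shown, and one summary sentence need not be a full list of its columns. The CHWs must hold at least some identifying particulars, since they pass them on for adults with uncontrolled BP. This stands. A reader might infer that the register has no age, no sex and no line for absent adults, but the protocol does not say so. On age and sex, the Appendix 2 heading points the other way, while sections 3.6 and 3.8 tie the form to enrolled participants. What can be said is that these passages need reconciling and that no record of non-response is provided for.

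Three further inferences are tempting and are not supported:
- *That there is a single screening round.* Section 3.5 gives no number of rounds or calls. It mentions no return visit to adults missed, but does not exclude one.
- *That the recruitment rate fails too.* Section 3.7 says "We will assess feasibility of the intervention by examining recruitment rates", and recruitment runs from adults screened, referred and traced. That denominator is available without counting adults never reached.
- *That non-response could never be seen or corrected.* An outside count of ward adults, if one exists, would show overall response, and weighting would be possible if age and sex are recorded.

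It can also be said that form layout is operational and that weighting belongs in an analysis plan. The choice of weights does. What is collected at the door is a protocol matter, and section 3.5 is where it is described. Finally, the illustrated sizes rest on assumed inputs, and the low end of 1 point lies inside the ±1.9. That is correct.

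**Conclusion.** The concern holds in a limited form. Objective i names all adults in the wards, and the protocol does not provide for counting those who are absent or refuse, nor clearly for recording age and sex of everyone screened. Followed as written, it yields a prevalence among adults found and willing, with non-response not assessable from the trial's own data.

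Neither the size nor the direction of bias can be derived from the documents. The 1 to 6 points show only that, under plausible assumed response and gap, the bias could exceed the sampling error. They do not show that the estimate will be wrong by that amount. The point bears on one of four specific objectives and leaves the randomised comparison untouched. It is a cheap improvement, worth making before screening starts because the information cannot be recovered from the register afterwards.

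**What to change.** In section 3.5, state that the register lists each resident adult with age, sex and result of the call (measured, absent, refused). Report the response proportion by ward. Give prevalence weighted to the enumerated age-sex structure, Σ (N_g / N) × p_g over age-sex groups g, beside the crude figure. Here N_g is the number of resident adults listed in group g, N is their total, and p_g is the prevalence among those measured in group g. State also whether the Appendix 2 questionnaire is used at screening or only for trial participants, so that its heading agrees with sections 3.6 and 3.8.

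If the form already holds these fields, a sentence in section 3.5 saying so closes the recording gap. If it cannot be changed, restate objective i, and the matching research question in section 2.1, as prevalence among adults present and willing at the door-to-door screening.

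The cost is three entries per adult and slightly more CHW time per household. Weighting by age and sex will not remove differences within those groups, for example by work, so the response proportion should be shown with the weighted figure.
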